## Discussion

The *Family Matters* intervention has high potential public health impact as it aims to change clinical practice by creating a new model of care for child CVH in primary care. Research in this field is needed given the low to moderate success of lifestyle behavior interventions for children at risk for CVD and the persistent high prevalence of disparities across race/ethnicity groups. The state-of-the-art measures being used including EMA, EMI, and video feedback combined with the novel intervention context of family meals and CHWs as interventionists will greatly advance the field. In addition, the three-arm study design will allow for testing which combinations of intervention components are most effective in improving child CVH by race/ethnicity as well as whether a virtual or hybrid Arm is more effective. Dependent on study findings, this intervention will be disseminated to other primary care settings.

## Figures and Tables

**Figure 1 F1:**
[figure not shown]
Family Matters Intervention Study.

**Figure 2 F2:**
[figure not shown]
The SPIRIT diagram

**Figure 3 F3:**
[figure not shown]
The Family Matters Intervention Flowchart.

**Table 1: T1:** Family Matters Intervention Primary and Secondary Outcome Measures and EMI Survey Questions Used in Intervention.

Primary Outcome Measures	
**Child BMI%ile**	Child BMI percentiles (%ile) was used as a primary outcome based on prior evidence that a change in BMI%ile was associated with lower risk of hypertension, dyslipidemia, hypertriglyceridemia, and HDL (risk factors for metabolic syndrome and cardiovascular disease) in children with overweight or obesity [46]. **Procedure:** Objectively measured child height and weight are collected via a virtual visit over Zoom. Families are sent a digital scale and measuring tape. Families watch a short training video on how to take heights and weights. After the video, trained and certified research staff guide parents/guardians on taking the child’s height and weight using standardized protocols [43]. To ensure reliability, all measures are taken twice: height measurements need to be within 0.5 cm of each other, and weight measurements need to be within 1.0 lbs of each other. **Measure**: BMI%iles are calculated using Centers for Disease Control and Prevention (CDC) sex-specific BMI-for-age growth charts [43]. BMI%iles were chosen given the issue of BMI z-scores being a less sensitive measure when children are >95^th^ BMI%tile [46].
**Child Neck Circumference**	Neck circumference (NC) has been shown to be highly associated with cardiovascular disease in children [47] and adults [47], and is strongly correlated with waist circumference [47]. NC is often chosen over other measures (e.g., waist circumference) as it is not impacted by respiratory movement or postprandial abdominal distension, is non-invasive, does not require clothing removal, and is easy to collect [47] **Procedure**: Families are sent a 24” measuring tape prior to their virtual visit to collect NC. Families watch a short training video on how to take NC. After the video, trained and certified research staff guide parents/guardians on taking the child’s NC using standardized protocols. **Measure:** Locate the prominence on the neck (i.e, Adam’s apple), and wrapping the measuring tape around the child’s neck directly under this prominence. The research staff confirm the child is looking straight ahead and that the measuring tape is straight. To ensure reliability, NC measurements are taken twice and measurements need to be within 0.5 cm of each other.
**Child Diet Quality**	Child diet quality was used as a primary outcome given its link to child risk for heart disease and obesity in adulthood. **Procedure:** Three 24-hour dietary recalls (2 weekdays, 1 weekend day) [48] are conducted using the *Nutrition Data System for Research (NDS-R)* [61] regarding the child’s dietary intake. Following best practice guidelines [61], recalls for children <6 years old are done with only the parent. For children >6 years old, recalls are done with both the child and parent; the parent is the main reporter for children 6-8 years old, and the child is the main reporter for children 9+ years old [48]. **Measure:** The first recall is conducted during the virtual visit, and the 2^nd^ and 3^rd^ recalls are scheduled and conducted virtually during the 2-week period following the virtual visit. To increase accuracy of reporting, families are sent a Food Amounts Booklet to measure amounts, school lunch menus are utilized, and parents/children are encouraged to complete a food diary prior to the scheduled recall. An overall *Healthy Eating Index* (*HE*I) [49] score that measures overall diet quality/healthfulness will be calculated for analyses using data from 24-hour dietary recalls.
Secondary Outcome Measures	

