### Inclusion Criteria:

Children ages 5-10, their primary caregiver (e.g., parent, grandparent, aunt) and at least one sibling.Children at high risk for CVD, defined as BMI ≥75th percentile [43].Children from African American/Black, Asian, Hispanic, Native American, or White households who speak Spanish or English.Children who consume ≤3 family meals per week [12].

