### Sample Size and Power Computations.

Study design features were accounted for in powering the study that required increases in sample size to minimize an inflated experiment-wise error rate (EER) due to three pairwise tests between each treatment arm for three primary outcomes (i.e., BMI%ile, neck circumference, and the Healthy Eating Index (HEI)). Accounting for these nine tests, sample size was determined using a conservative two-sided critical value of *z*=2.77 (*P*=0.006) to achieve experiment-wise Type I error of 0.05. Our power calculations were based on prior studies showing that a decline of two BMI%ile points was a clinically meaningful difference in children with overweight/obesity [46]. BMI%ile is a continuous outcome with a variance of 18.8. Eighteen-month follow up data with a comparable cohort provided intraclass correlation coefficient estimates to inform sample size determination (BMI%ile ICC ). At 80% power and multiple-outcome and pairwise testing corrected EER of 0.05, with a sample size of 525, we will be able to detect a minimum average difference in BMI%ile as small as 1.67 (or 0.38 SD) with 15% attrition. This magnitude translates to approximately a 2.8lb difference in a six year-old boy who is 3.8 feet tall and 45 lbs, or approximately a 7.5 ounce per month change in weight by the post-intervention endpoint.

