#### Sub-group Exploratory Analyses:

Analyses exploring whether interaction effects depend on participant sex, race/ethnicity, and seasonality will also be conducted. These post-hoc analyses will examine whether the intervention has synergistic effects in specific populations or during different seasonal contexts. Post-hoc analyses will be conducted to explore the interaction of child/parent sex and baseline weight status on intervention treatment effects to determine whether the intervention is particularly effective in certain subpopulations.

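### The reason given for preferring BMI percentile to the z-score is reversed, because percentiles flatten more in the upper tail, and equating 1.67 points with 2.8 lb fails over most of the eligible range

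*Protocol article*

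**What the plan says.** Table 1 (Child BMI%ile) gives two reasons for the outcome. The first is prior evidence linking change in BMI percentile to cardiometabolic risk. The second is the comparison with z-scores: "BMI%iles were chosen given the issue of BMI z-scores being a less sensitive measure when children are" above the 95th percentile. The source of the percentile is stated: "BMI%iles are calculated using Centers for Disease Control and Prevention (CDC) sex-specific BMI-for-age growth charts".

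The Inclusion Criteria set a floor and no ceiling: "Children at high risk for CVD, defined as BMI ≥75th percentile".

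Sample Size and Power Computations takes a fall of two percentile points as clinically meaningful. It states "BMI%ile is a continuous outcome with a variance of 18.8" and gives a detectable difference of 1.67 points (0.38 SD). It then adds: "This magnitude translates to approximately a 2.8lb difference in a six year-old boy who is 3.8 feet tall and 45 lbs", or about 7.5 oz per month to the post-intervention endpoint.

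Sub-group Exploratory Analyses plans to "explore the interaction of child/parent sex and baseline weight status on intervention treatment effects".

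**The concern.** On one growth chart, percentile and z-score are the same measurement in different units. The conversion is steep near the median and almost flat in the upper tail. If z is too insensitive above the 95th percentile, the percentile must be more so, and the plan's second reason points the wrong way.

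Three things are at stake:

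- The mean difference in points gives little weight to the heaviest children, in a trial aimed at children at raised cardiovascular risk.
- A weight-status interaction analysed on percentiles could suggest less benefit in heavier children when the effect on z is the same in all of them.
- Readers are told that the detectable difference corresponds to a weight change that, over most of the eligible range, is far larger than 1.67 points represents.

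**Working it through.** **1. The plan's own figures.** Inputs from Sample Size and Power Computations: critical value 2.77, 80% power (z = 0.842), variance 18.8 (SD 4.336). From Study Arms and Randomization: 175 per arm.

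Detectable difference = (2.77 + 0.842) × 4.336 × √(2/175) = 1.674, against the stated 1.67; 1.67/4.336 = 0.385 SD, against the stated 0.38. This match uses 175 per arm with no loss. Whether the ICC, whose value is missing from the text at hand, absorbs the 15% attrition is a separate matter and is not used here.

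2.8 lb × 16/6 = 7.47 oz per month, so the step from pounds to ounces per month is correct.

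**2. Slope of the percentile scale.** Percentile = 100·Φ(z), so points per z unit = 100·φ(z). This needs no outside figure.

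| Starting percentile | z | Points per z unit | Relative to 75th | Points for a 0.1 z fall | z change equal to 1.67 points |
|---|---|---|---|---|---|
| 75th | 0.674 | 31.8 | 100% | 3.28 | 0.052 |
| 85th | 1.036 | 23.3 | 73% | 2.45 | 0.069 |
| 95th | 1.645 | 10.3 | 32% | 1.12 | 0.144 |
| 98th | 2.054 | 4.8 | 15% | 0.54 | 0.263 |
| 99th | 2.326 | 2.7 | 8% | 0.30 | 0.395 |
| 99.9th | 3.090 | 0.34 | 1% | 0.04 | 0.99 |

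Every eligible child starts on the falling part of this curve.

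**3. The weight translation, by a simple route.** Height is 3.8 ft = 45.6 in. BMI = 45 × 703/45.6² = 15.2 kg/m². Taking off 2.8 lb gives 42.2 × 703/45.6² = 14.3, a fall of 0.95 kg/m² (2.8/45 = 6.2%). If 0.95 kg/m² is to equal 1.67 points, the BMI SD must be 0.947 divided by the last column above:

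- 75th: 0.947/0.0517 = 18.3 kg/m²
- 85th: 0.947/0.0691 = 13.7 kg/m²
- 95th: 0.947/0.144 = 6.6 kg/m²

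The boy's entire BMI is 15.2, so the first of these exceeds it and the second nearly equals it.

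**4. The same check allowing for skew.** The CDC curve parameters are not in the document, so a range is assumed: BMI = M(1 + L·S·z)^(1/L), with L from +1 to −3 and S from 0.07 to 0.12. At fixed height, percentage change in weight equals percentage change in BMI, and M cancels.

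| Starting percentile | Points for 2.8 of 45 lb | Pounds for 1.67 points |
|---|---|---|
| 75th | 16–35 | 0.16–0.36 |
| 85th | 10–32 | 0.20–0.58 |
| 95th | 3–21 | 0.41–1.76 |

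In no combination does 2.8 lb equal 1.67 points at the 75th, 85th or 95th percentile. The two meet only from about the 97th percentile (most skewed, widest curve) to beyond the 99.9th (symmetric, narrowest curve).

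**The case against.** The strongest reply is that the z-score sentence is only one of two reasons. Table 1 first cites evidence tying change in BMI percentile to cardiometabolic risk, and the two-point threshold comes from the same source. The variance and detectable difference are also stated on the percentile scale, so the choice of scale does not by itself make the power calculation wrong. The weight illustration does not enter that calculation. Neck circumference, a co-primary outcome without a percentile ceiling, is measured in the same children. All of this stands. It argues against replacing the primary outcome, but it does not rescue the sentence or the illustration.

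A reader might go further in four ways that the document does not support:

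- **All children above the 95th percentile barely count.** At the 95th the weight is still about a third of that at the 75th; the phrase fits from about the 98th. No baseline distribution is given, so the number of such children is unknown.
- **A fixed share of statistical efficiency is lost.** The result depends on the assumed population. Relative to z, with change scores, efficiency is 0.78–0.79 if baseline z has mean 0.6 and SD 1.1 cut at the 75th percentile, and about 0.9 with mean 0 and SD 1. It falls to about 0.45 if the effect is proportional to z.
- **The interaction will show less benefit in heavier children.** That assumes an equal z effect and a BMI percentile outcome. The section names no outcome and labels these analyses exploratory and post hoc.
- **The 9.6 oz per month under Other Exploratory Hypotheses is also wrong.** It belongs to a different, moderation model, and its derivation is not shown. Its basis needs checking; no error has been demonstrated.

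**Conclusion.** The point holds in two parts.

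First, the stated advantage over z-scores is reversed. This is a mathematical fact about percentiles and rests on no assumption. Per unit of z, a child at the 95th percentile moves the outcome about 32% as much as a child at the 75th, and a child at the 99th about 8%. An equal z effect would therefore appear smaller in heavier children in any interaction run on BMI percentile.

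Second, equating 1.67 points with 2.8 lb, and so with 7.5 oz per month, is wrong for starting percentiles from the 75th to about the 97th. At the 75th percentile 2.8 lb is roughly 8 to 18 times too large (2.8/0.36 to 2.8/0.16). At the 95th it is about 1.6 to 7 times too large (2.8/1.76 to 2.8/0.41). These multiples depend on the assumed L and S range. The failure at the 75th, 85th and 95th holds throughout it. No single pound equivalent exists unless the starting percentile is stated, and the document does not state one for this boy.

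The documents do not establish that the primary outcome must be replaced or that the sample size is wrong because of the scale.

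**What to change.** 1. Correct the rationale sentence in Table 1. The choice can rest on the cited evidence for change in BMI percentile, with its upper-tail compression acknowledged.
2. Keep BMI percentile as the registered primary outcome. Before unblinding, prespecify a key supporting analysis on an uncompressed scale from the same heights and weights: BMI as a percentage of the age- and sex-specific 95th percentile, or BMI adjusted for baseline BMI, age and sex.
3. Run any BMI-based weight-status interaction on that scale.
4. Recompute 2.8 lb and 7.5 oz per month from the CDC tables at a stated eligible starting percentile, or delete them. Check and state the basis of the 9.6 oz per month figure.

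No new measurements are needed. The cost is some added analysis and text, and a less favourable weight illustration. Making the uncompressed scale primary would be a larger step: recruitment is under way, and the threshold, variance, ICC and detectable difference would all need new inputs that the document does not give.

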**Family-Level Outcomes**	
**Family Meal Quantity**	Family meal quantity was measured as frequency of meals to match prior validated and reliable measures. **Procedure:** Self-report online survey. **Measure:** Parents are asked to report the number of people living in their home. They are then asked to say Yes/No to the following question for each day of the past week: “In the past 7 days, did you have a family dinner meal where at least [# of people in home – 1] – [# of people in home] people were sitting and eating at a table? The online survey is designed to tailor the days of the past week depending on the day the parent is taking the survey. For example, if the parent is taking a survey on a Tuesday and has 5 people in the home, they will be asked about frequency of family dinner meals where at least 4-5 people are present for: Last Tuesday, Last Wednesday, Last Thursday, Last Friday, Saturday, Sunday, and Yesterday.
**Family Meal Quality**	Family meal quality **consists of both dietary quality and interpersonal quality**. These two factors will be measured via video-recorded (via Zoom) family meals as well as ecological momentary assessment (EMA). **Procedures:** · **Video recorded family meals:** Following their virtual visit, families are asked to record two family dinner meals (1 weekday, 1 weekend day) over the next 2 weeks where the majority of the family is present. Our prior research showed that video-recording two family meals, including one week day and one weekend day, was adequate for measuring dietary healthfulness and interpersonal atmosphere at family meals [7,45]. Families are sent a HIPAA-compliant Zoom link where they are able to log on when their meal begins; the link is set up so that recording starts immediately and the video is automatically uploaded to the cloud. At the start of the video, families are instructed to introduce everyone present at the meal and to say what is being served at the meal. · **Ecological Momentary Assessment:** At the virtual visit, staff members register parents for EMA [44], which includes asking about wake and dinner times on weekdays and weekend days. Parents are randomly texted three signal-contingent surveys during the day (determined by parent’s wake time) as well as a meal survey, which is scheduled to be sent a minimum of an hour after the parent reports usually having dinner. Parents use their own smartphone in order to receive texts and access surveys. Parents have 1 hour to finish the first three signal-contingent surveys and 4 hours to finish the meal survey sent at the end of the day. Following the virtual visit, parents have 14 days to finish 10 “complete” days of EMA; a complete day includes at least 2/3 signal-contingent surveys as well as the meal survey. If parents are able to consecutively finish 7 complete days, they earn a $25 bonus. · During the meal survey, parents are asked whether they had a family dinner meal. If they did, they are asked to complete a meal screener. This includes: 1) Listing all the food served at the dinner (e.g., tacos, tortilla chips, refried beans, fruit salad); 2) For each food served, asking about the components of each food, including: Fruits, Vegetables, Dairy, Meat Protein, Other Non-Meat Protein (e.g., tofu), Whole grains, Refined grains, Snack Foods, and Desserts. If a participant selected Vegetables, Dairy, Meat Protein, Snack Foods, Desserts, and/or Sauces, they were asked to categorize the food even further. For example, if Vegetables was selected, the participant was asked if the food contained Dark Green Vegetables (e.g., kale, romaine lettuce, broccoli), Other Vegetables (e.g., corn, tomatoes, peas, potatoes), Fried Vegetables (e.g., French fries), and/or Pickles or olives. · Parents were also asked to report all of the drinks served at dinner, including: Water, Skim/low-fat milk, 2% or whole milk, Non-dairy drinks (e.g., soy milk), Tea, Coffee, Sports drinks, Fruit drinks (e.g., SunnyD), Regular pop/soda, Diet pop/soda, 100% fruit juice, No drinks were served, or None of the above. **Measures:** · **Meal Dietary Quality**. An adapted Healthfulness of Meal (HOM) index [21] is used to measure the dietary quality of foods served at family meals via the EMA meal screener. The HOM index is a quantitative coding system used in prior studies [21]. It was developed based on the Healthy Eating Index (HEI)-2015, which includes 13 components that are either adequacy components (food groups/subgroups that are encouraged) or moderation components (food groups where lower intake is encouraged.) Like the HEI-2015, points are given for the presence of some food components (e.g., Dark Green Vegetables), and the absence of other food components (e.g., Desserts). Higher scores represent a meal with higher dietary quality. · **Meal Interpersonal Quality.** The Iowa Family Interaction Ratina Scales (IFIRS] [50] will be used to measure the interpersonal interactions that occur at the two video-recorded family meals. The IFIRS is a quantitative direct observational coding system that measures behavioral and interpersonal interactions (e.g., dyadic, family level) [50]. IFIRS scales have been used with diverse families and have high validity (r=.77-.86) [50]. Example measures include: parent feeding practices (i.e., restriction, pressure-to-eat), parenting style (i.e., authoritative, authoritarian, permissive, neglectful), and family functioning (e.g., communication, conflict). Higher scores (range 1-9) represent healthy interpersonal dynamics.
**Parent-Level Outcomes**	
**Parent BMI**	**Procedure:** Parent height and weight are taken during the virtual visit using the same procedures as child height and weight. **Measure:** BMI values are computed according to the following formula: weight (kg)/height (meters)^2^ and cut offs for weight status are calculated using CDC guidelines [51].
**Parent Neck Circumference**	**Procedure**: Parent NC is taken during the virtual visit using the same procedures as child NC. **Measure**: The same measure as child NC is used.
**Food Parenting Practices**	**Procedure:** Food parenting practices are assessed via an on-line survey completed by the parent after the virtual visit as well as through the EMA meal survey. **Measure:** Parents are asked about a broad range of food parenting practices [52], which measure structure, autonomy support, coercive control, and indulgent feeding practices [52]. In the on-line survey, parents are asked about the frequency in which they engage in these food parenting practices; in EMA, they are asked (Yes/No) if they engaged in the food parenting practice at the meal that evening.
**Parent Coping Skills**	**Procedure:** Self-report on all four EMA surveys (three signal-contingent and the meal survey). **Measure:** Parents are asked to report on their current stress level (How would you rate your level of stress right now?), coping ability (How would you rate your ability to manage stress right now?), and current sources of stress (Childcare, Job dissatisfaction, Body image/weight concerns, Too many things to do).
**Sibling-Level Outcomes**	
**Sibling BMI%ile**	**Procedure:** Sibling height and weight are taken during the virtual visit using the same procedures as child height and weight. **Measure:** Sibling BMI%iles are calculated using the same procedures as child BMI%ile.
**Other Secondary Outcomes and Sub-analysis Variables**	
	**Procedure:** Other sociodemographic and home environment variables will be measured via validated self-report online measures. **Measures:** Socioeconomic status [53], race/ethnicity [8], sex and gender [54], education [55], acculturation [56], food security [57], food preparation [59], food purchasing behaviors [58,59], media use at mealtimes [13], work/family balance [62], household chaos [39], weight talk [55], and psychosocial factors [60].
**Ecological Momentary Intervention (EMI) Survey Items and Tips Used During the Intervention**	
**Stress Level, Source of Stress, and Helpful/Unhelpful EMI Survey Items**	During the active intervention phase (16 weeks), participants receive a daily text message on their phones with a link to a survey inquiring about: (1) Their level of stress (rating 0-10); (2) Ability to manage stress (rating 0-10); (3) Source of stress–19 potential categories of momentary stressors including (select all that apply): *1.* *Conflicts or arguments* *2.* *Demands from family* *3.* *Traffic/transportation problems* *4.* *New/current events* *5.* *Feeling conflicted over what to do* *6.* *Money for the things you need* *7.* *Too many things to do* *8.* *Job dissatisfaction* *9.* *Upcoming family events* *10.* *Unexpected change in plans* *11.* *Childcare* *12.* *Body image/weight concerns* *13.* *Fatigue* *14.* *Health issues (you own or others’)* *15.* *Interaction on social media* *16.* *Not sure what to serve for dinner* *17.* *Concerns about my child (e.g., wellbeing, behavior problems)* *18.* *Concerns about COVID-19* *19.* *No stress (general tips about family meals)* (4) Primary source of stress (select one option from previous list of sources); and (5) Whether or not the tip they received the day before was helpful. During the maintenance phase (8 weeks), participants receive the same survey 3x/week on the 3 days they reported highest stress levels.
**EMI Tips sent to Participants via Text Message during the intervention**	Tips are sent as text messages to participants based on their reported primary source of stress. A minimum of 50 tips are included in each of the 19 source of stress categories. Tips include affirmations, helpful links/apps, general tips for having family meals including recipes, and games to play at mealtime.

**Table 2: T2:** Training, Certification, Recertification, and Ongoing Supervision for Measurement Team Members and Intervention Community Health Workers.

